### Sample Size

A total of nine patients will be enrolled in the study. The study was planned using Simon’s minimax two-stage phase design [20]. The hypothesis to be tested was H0: P < P0 vs H1: P > P1, where P is the probability of mortality at 30 days, accepting a false-positive rate (*α*) ≤ 10% and a false-negative rate (*β*) ≤ 10%, and P0 was set to 50% and P1 was set to 90%. These parameters lead to a two-stage design with the first stage of four patients stopping if two or fewer survive, or continuing accrual to a total of nine patients, declaring success if more than seven patients survive.

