### Study Objectives and Endpoints

The primary objective of this first-in-human trial (NCVC-BTD_01) is to assess the safety and effectiveness of the BR16010 to support one or both sides of the heart as a BTD VAD for patients with severe heart failure or refractory cardiogenic shock refractory to optimal medical management, standard surgical procedures, or mechanical circulatory supports [e.g., intra-aortic balloon pumping (IABP), ventriculo-arterial bypass (VA bypass), and percutaneous cardiopulmonary support (PCPS)]. The study had a single set of entry criteria for patients designated for bridge to recovery (BTR) or bridge to transplantation (BTT).

The primary endpoint is a composite of survival free of device-related serious adverse events and complications during device support. For left ventricular assistance, withdrawal of a trial device due to cardiac function recovery or exchange to other VADs for the purpose of BTT during 30 days after implantation will be considered study successes. For right ventricular assistance, withdrawal of trial device due to right ventricular function recovery within 30 days after implantation will be considered a study success.

Secondary endpoints include changes in brain natriuretic peptide (BNP) levels (7 days after implantation of a trial device and the day of withdrawal of a trial device), period of mechanical ventricular support, changes in left ventricular ejection fraction (LVEF) (7 days after implantation of a trial device and the day of withdrawal of a trial device), and changes in left ventricular diastolic dimension (LVDd) (7 days after implantation of a trial device and the day of withdrawal of a trial device).

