**Fig. 3 Fig3:**
[figure not shown]
Summary of the study design

**Table 2 Tab2:** Data to be collected as part to of this study

Variables	Screening (baseline)	1–7 days	14 days	21 days	30 days	Every 2 weeks after 30 days	At VAD removal	7 days after removal
Patient information								
Basic characteristics	○							
Vital signs	○	○	○	○	○	○	○	
Image examinations								
Electrocardiogram	○	○	○	○	○	○	○	
Ultra sound cardiography	○	○	○					
Chest X-ray	○							
Brain CT scan	○							
Blood examinations								
Blood cell counts, electrolytes, chemistry, coagulation, etc.	○	○	○	○	○	○	○	
Heart function								
NYHA classification (or Ross classification)	○	○	○					

*CT* computer tomography, *NYHA* New York Heart Association

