### Statistical Analysis

Analyses will be done in all patients recruited into the study as a primary analysis population. Patient demographic data, safety, and efficacy endpoints will be analyzed descriptively: continuous data were expressed as mean with SD or median with range (minimum and maximum), whereas categorical data were expressed as numbers with percentages. All reported confidence intervals will be two-sided with 95% confidence level, and especially for binary endpoints, an exact CI for the proportion is calculated using the Clopper-Pearson method. All analyses are performed according to a prespecified statistical analysis plan using SAS V.9.3 or later (SAS Institute). The statistical analysis plan will be prepared separately and finalized before database-locking.

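### The primary endpoint has two success statements that are never joined, so some patients are classed differently by each; the two-stage rule counts a third quantity, survival

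*Protocol article*

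**What the plan says.** All references are to the protocol article.

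- **Study Objectives and Endpoints, first statement:** "The primary endpoint is a composite of survival free of device-related serious adverse events and complications during device support".
- **Same section, left-sided support:** withdrawal for cardiac recovery or "exchange to other VADs for the purpose of BTT during 30 days after implantation will be considered study successes".
- **Same section, right-sided support:** "withdrawal of trial device due to right ventricular function recovery within 30 days after implantation will be considered a study success". Exchange is not listed for the right side.
- **Same section, scope:** the device is meant "to support one or both sides of the heart". No rule combines the left and right criteria.
- **Abstract:** repeats both success statements, again without joining them.
- **Sample Size:** the two-stage rule concerns a quantity P, "where P is the probability of mortality at 30 days". Its limits nevertheless count survivors: stop if two or fewer of the first four survive, and declare success if more than seven of nine survive. P0 is 50% and P1 is 90%.
- **Patient Enrollment and Study Schedule:** patients are followed to day 30 or to transplant, explant or death if earlier, and for 7 days after removal. Table 2 has a column headed "Every 2 weeks after 30 days".
- **Statistical Analysis:** endpoints are described, and binary ones get a two-sided 95% Clopper-Pearson interval. "The statistical analysis plan will be prepared separately and finalized before database-locking".
- **Ethics and Dissemination of Results:** four patients had been enrolled by the end of January 2018.

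**The concern.** A primary endpoint has to place every patient in one class. Here the first statement turns on events during support and the second on how and when the device came off. Neither refers to the other, and they differ for patients whom the plan itself foresees. Whoever analyses the data must decide how the two combine.

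The trial is open-label, at one centre, with nine patients. The stated deadline for the SAP allows that decision to be taken when most or all outcomes are known. What is at stake is the reported primary proportion and its interval, and whether readers can trust that the classification was fixed independently of the results.

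**Working it through.** **1. Patients under each statement.** Three ways of joining the statements are open: both required (AND), either sufficient (OR), or the first is the endpoint and the second only says that early removal is not a failure (CLARIFY).

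| Patient | First statement | Device-outcome statement | AND | OR | CLARIFY |
|---|---|---|---|---|---|
| Device-related serious event, then exchange for BTT by day 30 | not met | success | fail | success | fail |
| Alive, event-free, still supported at day 30 | met | not listed | fail | success | success |
| Event-free, transplanted directly by day 30 | met | not listed | fail | success | success |
| Biventricular, event-free, both sides exchanged for BTT | met | left listed, right not | no rule | success | success |

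No two readings agree on all rows. The first two rows are the clearest cases. The last two are classes that one definition should also settle.

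**2. Size for the reported proportion.** One patient is 1/9 = 11.1 percentage points. For x successes in n = 9, the Clopper-Pearson limits are the 0.025 quantile of Beta(x, 10 − x) and the 0.975 quantile of Beta(x + 1, 9 − x).

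- 7/9 = 77.8%: 40.0% to 97.2%
- 8/9 = 88.9%: 51.8% to 99.7%
- 9/9 = 100%: 66.4% to 100%

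Hypothetical example: seven patients are successes on every reading, one is of the first type in the table and one of the second. The same data give 7/9 under AND, 8/9 under CLARIFY and 9/9 under OR.

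**3. The two-stage rule.** With n1 = 4, continuing on 3 or 4, and success if the total exceeds r of 9:

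P(pass) = Σ over x = 3, 4 of C(4,x) p^x (1 − p)^(4 − x) × P(Bin(5,p) ≥ r + 1 − x)

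- r = 7, as written, p = 0.9: 0.2916 × 0.5905 + 0.6561 × 0.9185 = 0.7748. At p = 0.5 the result is 0.0195.
- r = 6, p = 0.9: 0.2916 × 0.9185 + 0.6561 × 0.9914 = 0.9183. At p = 0.5 the result is 0.0781.

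The sample size of nine and the first stage are therefore reproduced. The written final limit has 77.5% power, not the stated 90% or more; more than six of nine would meet both error rates. That is a separate matter. What counts here is that the rule counts survivors. In the example in step 2, if all nine are alive at day 30, the rule sees 9/9 under every reading.

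**4. If the rule were meant for the primary endpoint.** Then one classification at 7/9 would flip the conclusion. The chance of ending exactly there is P(pass, r = 6) − P(pass, r = 7):

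- true rate 90%: 0.9183 − 0.7748 = 14.3%
- true rate 80%: 25.2%
- true rate 70%: 0.4184 − 0.1960 = 22.2%

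As an assumption for illustration, take 90% survival and a share q of survivors who are event-free, with both required. The chance of exceeding seven of nine is then 77.5% at q = 1, 61.7% at 0.95, 46.7% at 0.9 and 23.4% at 0.8.

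**5. Observability.** Follow-up ends 7 days after removal. A device removed on day d gives planned follow-up to day d + 7, which reaches day 30 only if d is at least 23. A patient explanted on day 10 is followed to day 17.

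**The case against.** The strongest reply is that the statements need not conflict. The first can be the endpoint and the others a note that planned early removal is not a failure. That reading is coherent. But requiring both is coherent too, and the two disagree on the event-free patient still supported at day 30. The article chooses neither.

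A second reply is that the article is a condensed account and that the full protocol or SAP may define the endpoint. Finalising an SAP before database lock is also ordinary practice, and an independent board discusses all serious adverse events. This stands in part: it cannot be said that no full definition exists, or that anyone intends to choose a favourable one. It does not remove the problem in the stated text, which gives two unreconciled versions of the primary endpoint, in the abstract as well as the body.

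A reader might infer that the trial's conclusion hangs on one patient's classification, with a 14% to 25% chance of landing on the boundary. The document does not support that as it stands. The rule counts survivors, the cases in dispute concern endpoint class and not survival, and no test of the composite is stated. A reader might also infer that transplant or biventricular support is a contradiction. Transplant appears only as an end of follow-up, and different left and right criteria are a design choice. Both are unassigned classes, not contradictions.

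**Conclusion.** The point holds in this form: the primary endpoint has two unreconciled success statements, and a third quantity, 30-day survival (labelled mortality), drives the two-stage rule. Two foreseeable types of patient are classed differently by the two statements.

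Each such patient moves the reported primary proportion by 11.1 points. Between 7/9 and 8/9 the exact interval goes from including 50% to excluding it. That is a descriptive comparison only, because the 50% was set for survival. The go/no-go decision is affected only on the assumption that the two-stage rule is meant to count the primary endpoint. The conclusion rests on the article's wording alone; a fuller definition in a document not shown could resolve it.

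**What to change.** Reconcile the passages into one binary, patient-level definition that:

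1. says whether freedom from device-related serious events and from complications is required in addition to the 30-day device outcome;
2. assigns one class each to ongoing support at day 30, direct transplant and biventricular support (which class is the sponsor's choice, but it must be fixed);
3. uses a survival window that the planned follow-up can observe, given that it ends 7 days after removal;
4. states which endpoint the two-stage rule counts, and corrects the description of P to match.

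Put this in the protocol or a signed SAP before further outcomes are reviewed, not merely before database lock. Since four patients, the whole of the first stage, were already enrolled by the end of January 2018, disclose when the definition was fixed and what was known then.

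The cost is amendment wording, an earlier SAP signature and a possibly lower reported success rate. If the sponsor wants day-30 survival for every patient, follow-up after early removal would also have to be extended.

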## Device Description

### Novel Centrifugal Blood Pump with HLB

The newly developed temporary VAD consists of a disposable centrifugal pump with an HLB. The priming volume of the pump is 18 mL. The pump-and-motor unit is 64 mm in diameter, 131 mm in height, and weighs 635 g (Fig. 1). The impeller is embedded in the stationary casing and rotates with a narrow clearance at both ends. The blood film in this clearance serves as the journal bearing, which generates sufficient pressure to sustain the impeller and avoid mechanical contact with the stationary part. The pump, which was previously described elsewhere [18], achieved a flow rate of 5.0 L min against a pressure head of 400 mmHg at 5150 rpm of RS (Fig. 2). The performance of the pump can ensure a sufficiently high flow rate even in patients with severe heart failure. However, for left ventricular assist, the operation conditions require a flow rate of 5.0 L min against a pressure head of approximately 100 mmHg (without circuit resistance), which implies decreasing the RS of the pump. On the other hand, maintaining a higher RS was recommended to achieve stable operation of the pump with the HLB. Therefore, it was necessary to ensure that the RS required for left ventricular assist can be maintained under stable pump operation. We built several mock circuits to investigate the contribution of the resistance of the cannulas and extracorporeal circuit, and identified candidates expected to provide adequate resistance for maintaining the RS necessary for stable pump operation. In addition, we performed in vitro hemolysis testing of the pump under the condition assumed for use in left ventricular assist. The pumps were operated at several rotational speeds, maintaining a mean flow rate of 5.0 L min for 4 h. The calculated normalized indexes of hemolysis (NIH) were 0.0003 at 3000 rpm (*n* = 1) and 0.0042 at 2500 rpm (*n* = 1). The NIH was elevated between 2500 and 3000 rpm. Based on these results, we determined that the lowest RS acceptable to avoid hemolysis was 3000 rpm in consideration of securing sufficient range of safe.

**Fig. 1 Fig1:**
[figure not shown]
Components of the new temporary left ventricular assist system developed in this study and overview of the clinical setup

**Fig. 2 Fig2:**
[figure not shown]
The H-Q curve of the hydrodynamically levitated bearing pump of the new temporary left ventricular assist system developed in this study

### Cannula

A 1/2-in. flexible polyvinyl chloride (PVC) tube with a hard tip (35 mm in length) and a 12-mm diameter vascular prosthesis attached to a flexible PVC tube were used as the inflow and outflow conduits, respectively (Fig. 1).

### Extracorporeal Circuit and Metallic Connector

The extracorporeal circuit, which ran between the pump head and the cannulas, consisted of 70-cm-long and 3/8-in.-wide PVC tubes. Custom-made metallic connectors were used for connecting the cannulas and extracorporeal circuit, to minimize thrombogenesis (Fig. 1). All the blood-contacting surfaces of the circuit were coated with T-NCVC heparin coating (TOYOBO, Osaka, Japan).

## Patient Enrollment and Study Schedule

Inclusion and exclusion criteria are shown in Table 1. Patients with severe heart failure or refractory cardiogenic shock refractory to optimal medical management, standard surgical procedures, or mechanical circulatory supports (e.g., IABP, VA bypass, and PCPS) are candidates for the study. All patients are required to provide written informed consent. Considering that BTD is a medical emergency, written informed consent of the patient’s next of kin is accepted in patients who are unconscious by therapeutic reason. Patients are notified at enrollment of their freedom to abandon the study at any time without consequences.

**Table 1 Tab1:** Inclusion and exclusion criteria

Inclusion criteria	
(1) Serious heart failure or refractory cardiogenic shock due to the following diseases, which does not respond to optimal medication and mechanical support	
- Low cardiac output syndrome due to cardiac disorders (idiopathic, secondary or ischemic cardiomyopathy, or myocarditis)	
- Post-acute myocardial infarction circulatory failures (including mechanical complication or refractory arrhythmia)	
- Difficulty in withdrawal of mechanical circulatory support	
- Postoperative low cardiac output syndrome (including refractory arrhythmia)	
- Other cardiogenic circulatory failures (including refractory arrhythmia)	
(2) Fully recovery is not expected with optimal medication, standard surgical procedures, and mechanical circulatory support	
(3) Body weight not lower than 10 kg at the time of informed consent	
(4) NYHA IV (Ross IV for children less than 7 years old) and at least one of the following conditions	
- INTERMACS/JMACS profile status 1 or 1A	
- INTERMACS/JMACS profile status 2 or 2A	
- Currently supported with extracorporeal membrane oxygenation (ECMO) or percutaneous cardiopulmonary support device (PCPS)	
(5) Written informed consent of the patient or his/her relatives	
Exclusion Criteria	
(1) Unfavorable or technically challenging cardiac anatomy	
(2) Evidence of irreversible hepatic disease (except when the primary investigator deems it as a sign of acute heart failure)	
(3) Evidence of irreversible renal disease (except when the primary investigator deems it as a sign of acute heart failure)	
(4) Evidence of irreversible intrinsic respiratory disease (e.g., chronic pulmonary disease, acute respiratory distress syndrome) which needs mechanical respiratory support (except when the primary investigator deems it as a sign of acute heart failure)	
(5) Contraindicated for anticoagulation	
(6) Difficulty of 30-day observation is anticipated	
(7) Pregnant or suspected pregnant at time of study entry	
(8) Participating in another clinical trial at time of study entry	
(9) Deemed unsuitable by the primary investigator for other reasons	

The trial VAD is implanted within 3 days after study entry. Patients were followed to the primary endpoint at 30 days after implantation of trial VAD or other outcomes (transplant, explant, or death), whichever occurred first. Patients will be followed for 7 days after removal or until other outcomes. For enhancing patient safety, the enrollment is held after the fourth patient is registered until the independent safety board confirms the 7-day safety for the patients. A summary of the study design is shown in Fig. 3. The schedule of data to be collected is presented in Table 2.

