### Independent Safety Evaluation Board

The independent safety evaluation board is comprised of three individuals not involved in the study conduct who have expertise in multiple disciplines, including a cardiologist, a nephrologist, and a neurologist. All serious adverse events are reported to and discussed by the independent safety board, and the 7-day safety of the first four patients is evaluated.

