### Ethics and Dissemination of Results

The study is conducted in compliance with the Declaration of Helsinki, International Conference on Harmonization/Good Clinical Practices, and the International Organization for Standardization of medical devices for human subjects, known as 14155:2011, and in accordance with country-specific requirements.

The study protocol (NCVC-BTD_01) has been reviewed and approved by National Cerebral and Cardiovascular Center Institutional Review Board (approved on 7/30/2017). A clinical trial notification as a new medical device, much like a US investigational device exemption application, was accepted by the Japanese regulatory agency before it started. The study was registered in UMIN Clinical Trials Registry (UMIN-CTR; R000033243). After the first patient was enrolled on October 6, 2017, four patients have been enrolled in this study at the end of January 2018.

The results of this study will be submitted for publication in peer-reviewed journals.

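### The enrolment hold after patient 4 is released on 7-day safety, so it does not ensure that the stage-1 futility rule, which rests on 30-day survival, is applied before patient 5 is implanted

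*Protocol article*

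**What the plan says.** The Sample Size section of the protocol article names a Simon "minimax two-stage phase design" and describes "the first stage of four patients stopping if two or fewer survive"; otherwise accrual continues to nine. The stage-1 sentence gives no time point. The time point comes from the hypothesis, "where P is the probability of mortality at 30 days". Although P is called mortality, the rule counts survivors, so the values 50% (P0) and 90% (P1) are read here as 30-day survival.

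The section Patient Enrollment and Study Schedule sets one pause at the same four-patient boundary: "the enrollment is held after the fourth patient is registered until the independent safety board confirms the 7-day safety for the patients". It presents this as a patient-safety measure. The section on the Independent Safety Evaluation Board gives the board the matching task: "the 7-day safety of the first four patients is evaluated". Neither section mentions a 30-day survivor count, and no section says how the pause and the stage-1 rule fit together.

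The Ethics and Dissemination section reports that "four patients have been enrolled in this study at the end of January 2018", the first on 6 October 2017. The boundary had therefore been reached by that date.

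**The concern.** Two conditions apply at the same boundary. One is a survivor count that needs 30 days of follow-up. The other is a safety confirmation that needs 7. The article states a positive trigger for reopening enrolment, and that trigger is the 7-day one. This is therefore a mismatch between two stated rules, and not a detail left to a fuller document.

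The purpose of stage 1 is to limit how many critically ill patients receive a first-in-human device if it performs no better than P0. A centre that follows the stated hold literally may implant a fifth patient while the result that decides whether there should be one is still pending.

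**Working it through.** **Inputs.** From Sample Size: P0 = 0.50, P1 = 0.90, α ≤ 0.10, β ≤ 0.10, n1 = 4, stop if ≤ 2 survive, N = 9. From Patient Enrollment and Study Schedule: implantation within 3 days of entry, and a hold to 7-day safety. From Ethics and Dissemination: four patients between 6 October 2017 and the end of January 2018 (taken as 31 January, 117 days). The timing of deaths within 30 days is not given and is assumed below.

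**Reproducing the design.** Exact enumeration of two-stage designs under these limits gives the minimax solution as stop at ≤ 2 of 4 and N = 9, which matches stage 1 and the total. (The enumerated final cut-off is more than six survivors, not the printed more than seven. That is a separate matter.) At 50% survival:
- P(stop at stage 1) = P(X ≤ 2 | 4, 0.5) = (1 + 4 + 6)/16 = 11/16 = 0.6875
- Expected N = 4 + (1 − 0.6875) × 5 = 5.56

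**Length of the gap.** Counting the 7 days from implantation and assuming a prompt board decision, the hold can lift 7 to 10 days after patient 4 is registered. That patient's 30-day status is known at 30 to 33 days. The gap is 30 − 7 = 23 days.

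**What can be recognised when the hold lifts, at 50% 30-day survival.** Let d be the probability of death by day 7. The stop is certain once two of the four have died.
- Constant hazard: d = 1 − 0.5^(7/30) = 0.149
- Half of the 30-day deaths in week 1: d = 0.5 × 0.5 = 0.25

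*Patients 1–3 at day 30, patient 4 at day 7.* P(≥ 2 deaths among three) = 0.5 and P(exactly one) = 0.375, so P(stop recognised) = 0.5 + 0.375d:
- 0.5 + 0.375 × 0.149 = 0.56
- 0.5 + 0.375 × 0.25 = 0.59

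Against 0.69, the shortfall is about 0.09 to 0.13.

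*Worst case, all four at day 7 only.* P(stop recognised) = 1 − (1 − d)^4 − 4d(1 − d)^3:
- d = 0.149: 0.11
- d = 0.25: 0.26

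**Which case is closer.** The mean spacing is 117/4 = 29 to 117/3 = 39 days. With roughly even spacing, patient 3 is past day 30 when patient 4 reaches day 7, so the first case applies. Individual entry dates are not given, and the article sets no minimum spacing, so the worst case is permitted.

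**Patients entering in the gap.** Expected number: 23/39 = 0.6 to 23/29 = 0.8. With Poisson arrivals, P(at least one) = 1 − exp(−23/39) = 0.45 to 1 − exp(−23/29) = 0.55.

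**Error rates if the stage-1 stop is not applied.**
- Printed final rule (at least 8 of 9): two survivors of four plus five more is at most 7, so the stop cannot change the outcome. α = 0.0195 and power = 0.775 either way.
- Cut-off at least 7 of 9: α moves from 0.078 to 0.090 and power from 0.918 to 0.947.

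In both cases α stays below 0.10.

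**The case against.** The strongest defence is that the two conditions are compatible. Sample Size itself makes continued accrual depend on stage 1. The 7-day hold is described as an added safety measure, and nothing says that it replaces the survivor rule or opens stage 2. The article is also a condensation: the study-design figure is not shown, and the full protocol may state how the two combine. This stands as a limit on how firmly one can say that the plan lacks the link. It does not remove the mismatch, because the one reopening condition the article states is the 7-day one.

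The defence also disposes of several stronger readings that a reader might draw:
- *That the futility stop cannot operate.* It can. Two deaths before release already meet it, and the rule still applies once the outstanding 30-day results arrive.
- *That the chance of stopping falls from 69% to 11%.* This requires that none of the four has been followed past day 7, which is unlikely at the reported pace.
- *That five further patients would be exposed.* This requires the Sample Size rule to be ignored altogether. Fewer than one patient is expected in the 23 days.
- *That the design's error control fails.* The calculation above shows that it does not.

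**Conclusion.** The point holds as an unreconciled mismatch with a limited but real consequence. As written, the hold can be lifted about 23 days before the stage-1 result is complete. If 30-day survival is 50%, a stop due with probability 0.69 would be recognisable at release with probability 0.56 to 0.59 when only patient 4 is incomplete, falling to 0.11 to 0.26 in the least favourable case the text allows. The harm is exposure, not a false claim of success.

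The result depends on reading P as 30-day survival, on the assumed share of deaths in week 1, and, for the 0.56 to 0.59 range, on roughly even spacing of the first four patients.

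**What to change.** Reconcile Sample Size, Patient Enrollment and Study Schedule, and Independent Safety Evaluation Board. Keep the 7-day safety review and state that it is additional to stage 1. Add that patient 5 is not enrolled until the stage-1 survivor count is settled at 30 days for the first four. The hold ends earlier once three 30-day survivors are confirmed, and accrual stops once two of the four have died within 30 days. The existing board can confirm the count.

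Use the survivor count from Sample Size, not the composite primary endpoint, which also requires freedom from device-related serious adverse events. Because follow-up ends 7 days after device removal, state that vital status at day 30 is obtained for any patient whose device is removed before about day 23.

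The cost is at most about 23 further days of hold in a ten-month enrolment window (October 2017 to July 2018), and often none. If patients 1–3 have reached day 30, stage 1 is still open only when exactly one of them has died. The probability of that is 3 × 0.1 × 0.9² = 0.24 at 90% survival and 0.375 at 50%.
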